#### **1.5. Compliance**

This study will be conducted in compliance with this clinical study protocol, Good Clinical Practice (GCP), and all applicable regulatory requirements.

## 2. OBJECTIVES

**The primary objectives of this study are as follows:**

- To evaluate the safety and tolerability of escalating single and multiple doses of TLC-2716
- To characterize the single- and multiple-dose pharmacokinetics (PK) of TLC-2716 and its metabolite(s)

**The exploratory objectives of this study are as follows:**

- To evaluate the pharmacodynamics (PD) of liver X receptor (LXR) inverse agonism by TLC-2716 as measured by metabolic parameters including fasting lipids and serum biomarkers of *de novo* lipogenesis (DNL)
- To characterize TLC-2716 dose and/or exposure-response relationships for PD markers
- To evaluate exploratory biomarkers

### **3. STUDY DESIGN**

#### **3.1. Study Design Description**

This protocol describes a single- and multiple-ascending dose FIH Phase 1 study to evaluate the safety, tolerability, PK, and PD of TLC-2716 in healthy adult subjects.

The study will be conducted at a single Phase 1 center in New Zealand. A total of up to 150 subjects will be enrolled, including 100 subjects in Parts A and B, and up to 50 subjects in adaptive cohorts in Part C. Within each cohort, 10 subjects will be randomized, including 8 subjects randomized to TLC-2716 and 2 subjects to PTM. In single-dose cohorts in Parts A and in any Part C cohort evaluating a higher total daily dose than previously evaluated, safety and tolerability data collected through Day 2 from two sentinel subjects, one randomized to TLC-2716 and one to PTM, will be evaluated prior to dosing of the remaining subjects in each cohort.

An approximately even distribution of healthy male and non-pregnant, non-lactating female subjects 18 to 55 years of age, inclusive, will be enrolled in the study. Subjects may not participate in more than one cohort of the study. Following the completion of Screening and admission assessments, eligible subjects will be enrolled on Day -1.

The duration of dosing will be 1 day for the SAD cohorts in Part A and C, and 15 days for the MAD cohorts in Parts B and C, including PTM dosing on Day -1 for all subjects in MAD cohorts.

The overall study duration, post-screening, will be up to 18 days for Part A, and up to 32 days for Parts B and C.

This study will proceed in 3 parts, with progression within and between parts governed by reviews of safety and any available and relevant PK and/or PD data, and the application of stopping rules. The sponsor, in consultation with the investigator, may choose not to initiate any or all adaptive cohorts in Part C if deemed unnecessary based on observations in Parts A and B. The overall study design and the design of each part are described below, and the study schemas are presented in [Figure 1](#) for SAD cohorts in Parts A and C, and [Figure 2](#) for MAD cohorts in Parts B and C.

##### **3.1.1. Part A: Single-Ascending Dose [SAD] (Cohorts 1-5)**

Part A will evaluate the safety, tolerability, PK, and PD of single-ascending doses of oral TLC-2716 or placebo under fed conditions. Part A will proceed in up to 5 dose-escalation cohorts and will be governed by a review of safety, tolerability, and any available and relevant PK and/or PD data, and study-specific stopping criteria. Planned study treatments within each cohort are provided in [Table 2](#).

- Within each cohort, 10 unique subjects will be randomized 4:1 to receive either blinded TLC-2716 (N = 8) or PTM (N = 2). All study drugs in Part A will be administered in the morning following a standard meal.
- At the initiation of each cohort in Part A, prior to randomization of the entire cohort, two sentinel subjects will be randomized, one to TLC-2716 at the dose to be evaluated in the planned cohort, and one to corresponding PTM. Enrollment and randomization of the remaining eight subjects in each cohort will be determined upon evaluation of all safety and tolerability data through Day 2 for these two sentinel subjects.
- For cohorts 2-5, initiation of single-dose administration will be permitted after evaluation of cumulative blinded safety data, and any relevant and available PK and/or PD data up to and including Day 4, following single-dose administration of the previous cohort.

**Table 2. Treatments to be Administered in Cohorts 1-5**

| Cohort | Single Ascending Doses (Day 1)                                           |
|--------|--------------------------------------------------------------------------|
| 1      | 0.5 mg TLC-2716 (1 x 0.5 mg) or PTM capsule SD, fed                      |
| 2      | 2 mg TLC-2716 a (1 x 2 mg) or PTM capsule SD, fed             |
| 3      | 6 mg TLC-2716 a (3 x 2 mg) or PTM capsules SD, fed            |
| 4      | 12 mg TLC-2716 a (2 x 5 mg; 1 x 2 mg) or PTM capsules SD, fed |
| 5      | 20 mg TLC-2716 a (4 x 5 mg) or PTM capsules SD, fed           |

PTM = placebo-to-match; SD = single dose

a The planned doses may be modified based on the observed safety, tolerability, and any relevant and available PK and/or PD data. Any modified dose will be within 3-fold of a dose previously tested.

A schematic of the activities within Part A cohorts is shown in [Figure 1](#). Adaptive SAD cohorts in Part C will follow the same study schema.

**Figure 1. Study Schema – Part A, SAD Cohorts 1-5**

[figure not shown]

For each cohort, subjects will be randomized to 8 active and 2 placebo-to-match.

Part C (Cohorts 11-15): Adaptive SAD Cohorts will follow the same schema as in Part A and Adaptive MAD Cohorts will follow the same schema as Part B.

- a The planned doses may be modified based on the observed safety, tolerability, and any relevant and available PK and/or PD data. Any modified dose will be within 3-fold of a dose previously tested.
- \* Complete PE at Screening, Day -1, Day 4, and Follow-up visit at Day 15 ± 2; symptom-driven exam performed at other time points indicated.
- ¥ Safety labs on Day 1 to occur 12 hours after study drug dosing; 12-lead ECG on Day 1 to occur 2 hours after study drug dosing.

### 3.1.2. Part B: Multiple-Ascending Dose [MAD] (Cohorts 6-10)

Part B will evaluate the safety, tolerability, PK, and PD of multiple-ascending doses of oral TLC-2716 or placebo under fed conditions. Part B will proceed in up to 5 dose-escalation cohorts and will be governed by a review of safety, tolerability, and any available and relevant PK and/or PD data, and study-specific stopping criteria. Planned study treatments within each cohort are provided in [Table 3](#).

- Randomized, blinded (sponsor-unblinded), placebo-controlled, multiple-ascending doses of TLC-2716 in healthy subjects. An attempt will be made to enroll at least 3 subjects in each cohort with Screening TG ≥ 150 mg/dL and/or low-density lipoprotein cholesterol (LDL-C) ≥ 130 mg/dL.
- Within each cohort, 10 unique subjects will be randomized 4:1 to receive either blinded TLC-2716 (N = 8) or PTM (N = 2) QD for 14 days.
- Part B (Cohort 6) may be initiated after the evaluation of cumulative safety, tolerability, and any relevant and available PK and/or PD data from all subjects enrolled in Cohort 3 in Part A (up to and including Day 4).

- For Cohorts 7-10, dosing may be initiated after evaluation of cumulative safety, tolerability, and any relevant and available PK and/or PD data from all subjects enrolled in the previous cohort in Part B through Day 14.
- All study drugs in Part B will be administered in the morning following a standard meal.

**Table 3. Treatments to be Administered in Cohorts 6-10**

| Cohort | Day -1          | Multiple Ascending Doses (Days 1-14)                                  |
|--------|-----------------|-----------------------------------------------------------------------|
| 6      | PTM capsule SD  | 0.5 mg TLC-2716 (1 x 0.5 mg) or PTM capsule, fed                      |
| 7      | PTM capsule SD  | 2 mg TLC-2716 a (1 x 2 mg) or PTM capsule, fed             |
| 8      | PTM capsules SD | 6 mg TLC-2716 a (3 x 2 mg) or PTM capsules, fed            |
| 9      | PTM capsules SD | 12 mg TLC-2716 a (2 x 5 mg; 1 x 2 mg) or PTM capsules, fed |
| 10     | PTM capsules SD | 20 mg TLC-2716 a (4 x 5 mg) or PTM capsules, fed           |

PTM = placebo-to-match; SD = single dose

a The planned doses may be modified based on the observed safety, tolerability, and any relevant and available PK and/or PD data. Any modified dose will be within 3-fold of a dose previously tested.

### 3.1.3. Part C: Adaptive SAD and/or MAD (Cohorts 11-15)

Part C includes optional, adaptive cohorts to evaluate the safety, tolerability, PK, and PD of single- and/or multiple-ascending doses of oral TLC-2716 or placebo under fasted or fed conditions. Based on available safety, PK, and/or PD data generated in Part A and Part B, as applicable, doses for Part C (Cohorts 11-15) will be chosen, up to a total daily dose of 50 mg. Planned study treatments within each cohort are provided in [Table 4](#).

Part C will proceed in up to 5 dose-escalation cohorts and will be governed by a review of safety, tolerability, and any available and relevant PK and/or PD data generated from previous Part A, B, and/or C cohorts, as applicable.

- Randomized, blinded (sponsor-unblinded), placebo-controlled, single- and/or multiple-ascending doses of TLC-2716 with adaptive dose selection in healthy subjects. An attempt will be made to enroll at least 3 subjects in each cohort with Screening TG  $\geq$  150 mg/dL and/or low-density lipoprotein cholesterol (LDL-C)  $\geq$  130 mg/dL.
- Within each cohort, 10 unique subjects will be randomized 4:1 to receive up to a total daily dose of 50 mg TLC-2716 (N = 8) or PTM (N = 2) for either 1 day (as in Part A) or 14 days (as in Part B).

The frequency of dosing (QD or BID in MAD cohorts) and fasting versus fed status (in SAD or MAD cohorts) may also be modified versus Parts A and B. If dosing is administered in the fed state, standard meal conditions may also be modified at sponsor discretion. QD doses will be administered in the morning following a standard meal, and BID doses will be administered after a standard morning meal and evening snack, with the second dose administered 12 hours

(± 10 minutes) after the morning dose. Once determined, dose level, duration of dosing, frequency of dosing, and meal conditions will remain consistent within a cohort. For any MAD cohort in Part C with BID dosing, both morning and evening doses must be administered on Day 14.

Multiple-dose, adaptive cohorts in Part C may be initiated in parallel with previous cohorts if the total daily dose under evaluation is at or below a dose already evaluated in Part B. If the total daily dose in any cohort is greater than has been previously evaluated, then sentinel dosing including one subject randomized to placebo and one subject to TLC-2716 will be included. Randomization of the remaining eight subjects in the cohort will be based on evaluation of all safety and tolerability data through Day 2 for these two sentinel subjects. If doses chosen in 2 or more adaptive cohorts exceed the dose evaluated in a previous cohort in Part B, these cohorts will be conducted in a staggered manner (lowest dose first), with the same stopping rules applied (Section 3.3).

**Table 4. Treatments to be Administered in Cohorts 11-15**

| Cohort | Day -1 a      | Single Dose (Day 1) or
Multiple Doses (Days 1-14)                                |
|--------|--------------------------|-------------------------------------------------------------------------------------|
| 11-15  | PTM capsule(s) QD or BID | ≤ 50 mg total daily dose TLC-2716 or PTM,
administered QD or BID, fasting or fed |

BID = twice daily; PTM = placebo-to-match; QD = once daily

a Dosing of PTM on Day -1 will only be performed in multiple-dose adaptive cohorts (as in Part B).

A schematic of the activities within MAD cohorts in Parts B and C is shown in [Figure 2](#).

**Figure 2. Study Schema – Part B, MAD Cohorts 6-10**

[figure not shown]

For each cohort, subjects will be randomized to 8 active and 2 placebo-to-match.

Part C (Cohorts 11-15): Adaptive SAD Cohorts will follow the same schema as in Part A and Adaptive MAD Cohorts will follow the same schema as Part B.

a The planned doses may be modified (reduced) based on the observed safety, tolerability, and any relevant and available PK and/or PD data. Any modified dose will be within 3-fold of a dose previously tested.

\* Complete PE at Screening, Day -2, Day 17, and Follow-up visit on Day 28 ± 2; symptom-driven PE on all other days of confinement.

\*\* All multiple-dose subjects in Part B and C will be administered PTM on Day -1.

‡ Safety labs on Day 1 to occur 12 hours after study drug dosing; 12-lead ECG on Day 1 to occur 2 hours after study drug dosing.

### 3.2. Dose Escalation Criteria

#### *SAD Cohorts in Parts A and C*

At the initiation of each single-dose cohort in Part A and in any single-dose cohort in Part C evaluating a higher total daily dose of TLC-2716 than previously evaluated, two sentinel subjects will be randomized, one to TLC-2716 at the dose to be evaluated in the planned cohort, and one to corresponding PTM. Enrollment and randomization of the remaining eight subjects in each cohort will be determined upon evaluation of all safety and tolerability data through Day 2 for these two sentinel subjects.

Initiation of single-dose administration at a higher dose will be determined by evaluation of safety and any relevant and available PK and/or PD data through Day 4 for all subjects enrolled in the previous dosing cohort.

### ***MAD Cohorts in Part B***

Dosing in Cohort 3 of the SAD portion of the study (Part A) will be completed prior to proceeding with the MAD portion of the study. Initiation of multiple dosing within Cohort 6 will be determined by a review of the cumulative safety, and any relevant and available PK and/or PD data through Day 4 of Cohort 3 in Part A.

Initiation of subsequent multiple-dose cohorts at a higher dose will be determined upon evaluation of all safety data, and any relevant and available PK and/or PD data through Day 14 from all subjects enrolled in the previous multiple-dose cohort.

In both Parts A and B, escalation to a dose higher than previously studied may occur only in the absence of dose-limiting toxicity and/or not meeting any prespecified stopping criteria.

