### Part B (MAD), Pre-specified Cohorts 6-10

Part B will proceed in up to 5 dose-escalation cohorts and will be governed by reviews of safety and tolerability, and any relevant and available PK and/or PD data, and study-specific stopping criteria. Within each cohort, 10 unique subjects will be randomized 4:1 to receive either blinded TLC-2716 (N = 8) or PTM (N = 2) QD for 14 days.

All study drugs in Part B will be administered in the morning following a standard meal.

Part B (Cohort 6) may be initiated after the evaluation of cumulative safety, tolerability, and any relevant and available PK and/or PD data from all subjects enrolled in Cohort 3 in Part A (up to and including Day 4).

For Cohorts 7-10, dosing may be initiated after evaluation of cumulative safety, tolerability, and any relevant and available PK and/or PD data from all subjects enrolled in the previous cohort in Part B through Day 14.

In both Parts A and B, escalation to a dose higher than previously studied may occur only in the absence of dose-limiting toxicity and/or not meeting any prespecified stopping criteria.

The cohorts and study treatments for Part B are as follows:

| Cohort | Day -1          | Days 1-14                                                             |
|--------|-----------------|-----------------------------------------------------------------------|
| 6      | PTM capsule SD  | 0.5 mg TLC-2716 (1 x 0.5 mg) or PTM capsule, fed                      |
| 7      | PTM capsule SD  | 2 mg TLC-2716 a (1 x 2 mg) or PTM capsule, fed             |
| 8      | PTM capsules SD | 6 mg TLC-2716 a (3 x 2 mg) or PTM capsules, fed            |
| 9      | PTM capsules SD | 12 mg TLC-2716 a (2 x 5 mg; 1 x 2 mg) or PTM capsules, fed |
| 10     | PTM capsules SD | 20 mg TLC-2716 a (4 x 5 mg) or PTM capsules, fed           |

PTM = placebo-to-match; SD = single dose

a The planned doses may be modified based on the observed safety, tolerability, and any relevant and available PK and/or PD data. Any modified dose will be within 3-fold of a dose previously tested.

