### ***Adaptive MAD Cohorts in Part C***

Based on safety and available PK and/or PD data from cohorts in Part A and Part B (if applicable), TLC-2716 doses for Part C may be chosen up to a total daily dose of 50 mg. If the total daily dose in any cohort in Part C is greater than has been evaluated in any prior cohort, then sentinel dosing including one subject randomized to placebo and one subject randomized to TLC-2716 will be completed. Randomization of the remaining eight subjects in the cohort will be determined based on evaluation of all safety and tolerability data through Day 2 for these two sentinel subjects. Additionally, if doses chosen in two or more adaptive cohorts exceed the dose evaluated in a previous cohort, those cohorts will be conducted in a staggered manner (lowest dose first), with the same stopping rules applied. Part C cohorts may be initiated in parallel with cohorts in Part B if the total daily dose under evaluation is at or below a dose already evaluated.

The sponsor, in consultation with the investigator, may choose not to initiate any or all adaptive cohorts if deemed unnecessary.

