## **5. STUDY DRUGS**

### **5.1. Randomization, Blinding, and Treatment Codes Access**

#### **5.1.1. Randomization**

It is the responsibility of the investigator to ensure that the subject is eligible for the study prior to enrollment and all enrollment criteria data are appropriately recorded. Subjects will be assigned a Screening number at the time of signing informed consent. Once a subject number has been assigned to a subject, it will not be reassigned to another subject. If necessary, replacement subjects may be enrolled (to compensate for early dropouts) after discussion and approval from the sponsor. A new unique subject number will be assigned to the replacement subject.

At Screening, study subjects will be assigned to Part A, B, or C, followed by assignment to a cohort within their respective part. Following confirmation of study eligibility on Day -1 (SAD cohorts) or Day -2 (MAD cohorts), eligible subjects will be randomized 4:1 to receive TLC-2716 or PTM and will be assigned a subject number. Note, for SAD cohorts in Part A and for any adaptive cohort in Part C evaluating a total daily dose that is higher than has previously been evaluated, two sentinel subjects, one randomized to TLC-2716 and one to PTM, will be evaluated through Day 2 prior to the randomization of the additional eight subjects in each cohort.

A randomization scheme including subject number and treatment assignments will be provided by the Sponsor to the unblinded study pharmacist for storing in a secure location. Blinded study site investigators and staff will not have access to this list. The study pharmacist, or designee, will remain unblinded throughout the study to allow for preparation of study drug.

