### 1.6.2. Part B (MAD), Cohorts 6-10

In Part B, up to 5 dose-escalation cohorts may be performed as outlined below. For Cohorts 7-10, dosing may be initiated after evaluation of cumulative safety, tolerability, and any relevant and available PK and/or PD data from all subjects enrolled in the previous cohort in Part B through Day 14.

| Cohort | Day -1          | Days 1-14                                                             |
|--------|-----------------|-----------------------------------------------------------------------|
| 6      | PTM capsule SD  | 0.5 mg TLC-2716 (1 x 0.5 mg) or PTM capsule, fed                      |
| 7      | PTM capsule SD  | 2 mg TLC-2716 a (1 x 2 mg) or PTM capsule, fed             |
| 8      | PTM capsules SD | 6 mg TLC-2716 a (3 x 2 mg) or PTM capsules, fed            |
| 9      | PTM capsules SD | 12 mg TLC-2716 a (2 x 5 mg; 1 x 2 mg) or PTM capsules, fed |
| 10     | PTM capsules SD | 20 mg TLC-2716 a (4 x 5 mg) or PTM capsules, fed           |

PTM = placebo-to-match; SD = single dose.

a The planned doses may be modified based on the observed safety, tolerability, and any relevant and available PK and/or PD data. Any modified dose will be within 3-fold of a dose previously tested.

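### Part B Cohorts 9 (12 mg) and 10 (20 mg) are not tied to single-dose clearance of the same dose in Part A and have no sentinel fallback: a minor gap that matters only if Part A falls behind, is cut short or is dosed lower

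*Combined protocol and SAP*

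**What the plan says.** **Entry to Part B.** Protocol Section 3.2 names one Part A milestone: "Dosing in Cohort 3 of the SAD portion of the study (Part A) will be completed prior to proceeding with the MAD portion". Cohort 6 then opens on the review of Cohort 3 through Day 4. Cohort 3 is planned at 6 mg (Table 2).

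**Steps within Part B.** Section 3.2 bases each higher multiple-dose cohort on all safety data, plus PK or PD data where available, "through Day 14 from all subjects enrolled in the previous multiple-dose cohort". Section 3.1.2 gives the same gate for Cohorts 7-10, using data "from all subjects enrolled in the previous cohort in Part B through Day 14". The synopsis and SAP Section 1.2.2 repeat it ("For Cohorts 7-10, dosing may be initiated after evaluation of cumulative safety, tolerability"), as does SAP Section 1.6.2. Planned doses in Table 3 are 0.5, 2, 6, 12 and 20 mg once daily for 14 days.

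**Conditions on escalation.** In Parts A and B, Section 3.2 bars going above a dose already studied if there is dose-limiting toxicity or a stopping criterion is met. Section 8.2.1 has all available safety data, and relevant PK and PD data, reviewed at each escalation.

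**Sentinels.** Section 5.1.1 requires a sentinel pair "for SAD cohorts in Part A and for any adaptive cohort in Part C evaluating a total daily dose that is higher" than any evaluated before. Section 3.2 puts the Part C rule this way: "If the total daily dose in any cohort in Part C is greater than has been evaluated in any prior cohort, then sentinel dosing" is used. Sections 3.1 and 3.2 give the same scope. None of them names Part B.

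**The concern.** Every planned Part B dose is also a Part A dose with its own sentinel pair, so the dose tables read as if each dose is meant to be given singly first. The written gates secure that order for Cohorts 6, 7 and 8 only.

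The protocol also treats similar situations differently. Suppose 12 mg is the highest dose given so far. A Part C cohort at 20 mg would have to begin with one active and one placebo subject. Part B Cohort 10, at the same 20 mg for 14 days, would not. This is a first-in-human trial in healthy volunteers, and the protocol lists sentinel dosing among its risk mitigations (Section 1.4).

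**Working it through.** **1. Which planned cohorts lack a required single-dose clearance.** Inputs: required clearance 6 mg (Cohort 3, Table 2); Part B doses from Table 3.

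- Cohorts 6, 7 and 8 (0.5, 2 and 6 mg): at or below 6 mg, so covered.
- Cohort 9: 12/6 = 2.0 times the required clearance, so not covered.
- Cohort 10: 20/6 = 3.33 times, so not covered.

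These are 2 of 5 Part B cohorts, or 2 x 8 = 16 of 5 x 8 = 40 planned active subjects. The 3-fold limit in the Table 3 footnote applies to modified doses and so does not gate the planned 12 and 20 mg.

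**2. Size of the steps.** From a dose already given for 14 days: 12/6 = 2.0-fold and 20/12 = 1.67-fold. Margins use the 336 mg human-equivalent monkey NOAEL in Table 1. At 20 mg, 336/20 = 16.8, which reproduces Table 1. At 12 mg, 336/12 = 28.

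**3. Planned calendar.** Inputs: sentinel pair reviewed through Day 2 and the other eight through Day 4 in each Part A cohort; Day 14 review in Part B; admission on Day -1 (single dose) or Day -2 (multiple dose), Section 3.5. No time is allowed for review or recruitment.

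*Back to back* (calendar day 1 = Cohort 6 Day 1 = Cohort 4 sentinel Day 1):
- Cohort 4: sentinels day 1, other eight day 3, their Day 4 on day 6.
- Cohort 5: sentinels day 7, other eight day 9, their Day 4 on day 12.
- Part B first active doses: days 1, 15, 29, 43 and 57.
- Lead: 43 - 6 = 37 days (Cohort 4 before 9); 57 - 12 = 45 days (Cohort 5 before 10).

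*Each group admitted the day after the preceding review* (day 1 = first day after the Cohort 3 review):
- Cohort 4: sentinels day 2, other eight day 5, their Day 4 on day 8.
- Cohort 5: sentinels day 10, other eight day 13, their Day 4 on day 16.
- Part B first active doses: days 3, 19, 35, 51 and 67.
- Lead: 51 - 8 = 43 days; 67 - 16 = 51 days.

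Part A is therefore ahead by 37/7 = 5.3 to 43/7 = 6.1 weeks for Cohort 9, and by 45/7 = 6.4 to 51/7 = 7.3 weeks for Cohort 10.

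**4. What a sentinel step would change if the gap opened.** The documents give no acute event rate, so p is an assumption, shown over 5% to 30%.

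- Chance of at least one event among eight active subjects, 1 - (1 - p)^8: 34%, 57%, 83% and 94% at p = 5%, 10%, 20% and 30%.
- Chance of an event in one active sentinel: p itself, 5% to 30%.
- Expected events with all eight dosed, 8p: 0.40, 0.80, 1.60 and 2.40.
- Expected events if a sentinel event stops the cohort, p + (1 - p) x 7p: 0.38, 0.73, 1.32 and 1.77.

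A single sentinel greatly reduces the chance of an event before the first review. It reduces the expected number of events only modestly when the rate is low.

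**The case against.** The strongest reply is that the safeguards already in place, and the calendar, leave little to fix.

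- **Review is broad.** The Part B gate calls for cumulative data, Section 8.2.1 for all available data, and toxicity in Part A bars escalation in Part B too. This stands. Someone might infer that Cohorts 9 and 10 open on the previous cohort's Day 14 review and nothing else; the documents do not support that. But these provisions act on data that exist. None requires 12 or 20 mg to have been given singly.
- **The contingencies are thin.** SAP Sections 1.4.1 and 1.6.1 treat all five Part A cohorts as going ahead, although protocol Section 3.1.1 sets five as a maximum. Parts A and B share the dose-modification footnote, so data that lowered a Part A dose would also be before those deciding on Part B. This makes the case unlikely. It does not place Cohort 4 before 9 or Cohort 5 before 10, and no text lowers a Part B dose when its Part A counterpart is lowered.
- **The added risk is limited.** Eight active subjects will already have had half (6 of 12 mg) or three-fifths (12 of 20 mg) of the dose for 14 days. Subjects are confined through Day 17 with laboratory tests on Days 1, 2, 3 and 5, and Section 3.3.2 can suspend dosing within a cohort. The documents do not give the within-cohort dosing schedule, so eight starting before any review is the most exposed case. This stands and keeps the severity low.
- **Part C differs.** Its doses are adaptive, reach 50 mg and have no planned single-dose lead-in, so a different sentinel rule is defensible while Part A stays ahead. That reasoning fails in the contingency at issue.
- **The schemas are not shown.** An order drawn in Figure 1 or 2 cannot be excluded; the finding is limited to the text.

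**Conclusion.** The point holds as a minor contingency safeguard. In the available text, Cohorts 9 and 10 may open without prior single-dose clearance of their dose and without a sentinel step. On the planned calendar nobody is affected. The gap opens only in one of three cases:

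- Part A slips by more than about 5 to 6 weeks (Cohort 9) or 6.5 to 7 weeks (Cohort 10) relative to Part B.
- Part A is shortened for a reason other than toxicity.
- Part A is dosed below plan while Part B is not. For example, if Cohort 5 were cut to 15 mg, Cohort 10 could still open at 20 mg; this route needs no delay.

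Eight active subjects per cohort would then be concerned, 16 at most. The calendar assumes no review or recruitment time and uninterrupted progress in both parts.

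Two stronger readings should be resisted. One is that the plan as scheduled sends 16 subjects to unscreened doses; the lead computed above contradicts it. The other is that Part B may exceed its planned doses unchecked. Table 3 speaks only of modification, but the Figure 2 footnote says "The planned doses may be modified (reduced) based on the observed safety, tolerability", so the text does not support a claim about doses above plan.

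**What to change.** Add to protocol Sections 3.1.2 and 3.2, and mirror in Section 5.1.1, the synopsis and SAP Sections 1.2.2 and 1.6.2:

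*A Part B cohort may start only if its dose does not exceed the highest single dose reviewed through Day 4 in Part A without meeting stopping criteria; otherwise it must begin with one active and one placebo sentinel subject reviewed through Day 2, as in Part C.*

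As planned, this places Cohort 9 after Cohort 4 and Cohort 10 after Cohort 5. It reuses the sponsor's own Part A clearance and Part C sentinel rules.

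The cost is one sentence and IRB/IEC approval of the amendment (Section 9.2.1), with no delay on the planned calendar. If Part A lags or is dosed lower, a Part B cohort either waits or uses two of its ten subjects as sentinels. In the latter case the other eight start on sentinel Day 3 at the earliest (2 days later), or on sentinel Day 5 if admitted only after the Day 2 review (4 days later).
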